## 2.2 Randomization and Blinding

There are 75 villages in the government comparison area and 67 villages in the intervention area. The villages in each area will be randomized separately. Infants in half of the villages in each area will be eligible to receive Rotarix during their EPI doses. In each area, villages will be randomly selected for Rotarix introduction after pre-stratifying on village size and baseline hospitalization rates/numbers for diarrhoea at the Matlab Diarrhoeal Hospital and community treatment centres during 2005 and 2006. Hospital charts for diarrhoea admissions will be reviewed to determine the number/rates of hospitalizations from those villages. The villages will be arranged sequentially based on diarrhoea admission number/rates to the Matlab and Nayergaon and Kalirbazaar treatment centres. For each stratum of villages, half of the villages will be randomly selected for introduction of Rotarix and the other half will for no introduction of Rotarix.

Although not a blinded evaluation, the introduction of bias will be reduced in several ways. First, the vaccine teams located in the EPI centres that are completely separate from the clinical settings where clinicians will be conducting surveillance. Second, the clinicians who treat the children when they present to a treatment facility are separated from those staff who carry out the vaccinations or conduct the laboratory testing. Third, the illness episodes are widely separated in

time from the vaccination, and thus the illness episode is not easily associated with receipt of vaccine. Fourth, laboratory assays for rotavirus will be carried out in the laboratory in Dhaka using coded specimens and are not conducted at the time of illness (since they have little clinical value). Although a parent could inform the clinician as to his/her child's participation in the study, this is believed to be an unlikely or important source of bias.

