We calculated sample size and power based upon a fixed number of events design and conditional on the total number of cases observed (Blackwelder, 1993; Chan 1998). The number of cases in each group was assumed to follow a Poisson distribution, with parameters  $\lambda_V$  for a vaccine villages and  $\lambda_U$  for the unvaccinated villages. Under this assumption, the number of vaccine cases,  $x_V$ , has a binomial distribution  $(X, P)$  conditional on  $X$ , the total number of cases, with  $P = \lambda_V / (\lambda_V + \lambda_U)$ . For the primary objective, we assumed 50% vaccine population (overall) effectiveness. With no design effect ( $DE=1$ ), observation of at least 77 admissions for rotavirus gastroenteritis among all age-eligible infants from vaccine and unvaccinated villages would ensure that the study has a minimum power of 80% to rule out a lower bound of 0% overall effectiveness. However, with a design effect of 3.48, a minimum of 268 admissions for rotavirus diarrhoea must be observed. Assuming a 3.5% total study-period attack rate in the unvaccinated villages, 268 admissions translates into an estimated minimum sample size of 10,210 infants (5105 in each group, vaccinated villages and unvaccinated villages) (Table 6).

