#### **Sample size for the immunogenicity subset**

We assume that the seropositive rate of the immunized children with Rotarix would be 60% and for the non immunized children be 35%. A sample size of 90 in each group would allow

detection of this difference with an alpha of 0.05, two-sided, and 90% power. Assuming a 10% loss to follow up, 100 subjects in each group are needed to meet the required sample size

**Table 6: Total sample size estimates to detect a reduction in population incidence of rotavirus diarrhoea hospitalizations for different population effectiveness and baseline incidence rate assumptions, different design effect (DE) values and different numbers of required endpoints (type II error of 5%, 2-sided and 80% power).**

| DE=3.48     | Vaccine Effectiveness       |           |           |          |
|-------------|-----------------------------|-----------|-----------|----------|
|             | 50%                         | 60%       | 70%       | 80%      |
| Incidence*  | Required number of outcomes |           |           |          |
|             | 268 cases                   | 164 cases | 104 cases | 59 cases |
| 4.00        | 8937                        | 5846      | 4016      | 2464     |
| 3.75        | 9528                        | 6229      | 4287      | 2631     |
| 3.50 | 10210                | 6675      | 4594      | 2819     |
| 3.25        | 10997                       | 7190      | 4942      | 3035     |
| 3.00        | 11909                       | 7788      | 5352      | 3285     |

\*RV admission rate per 100 children

(Assumes 1:1 randomization. Half of these totals sample sizes may receive Rotarix.)

During the planned course of the study (through March 2011), it is estimated that a total of approximately 11,650 infants will be born into both groups (5825 per group, section 2.3.3). While this estimated total study population is higher than that required to achieve 80% power (10,210), if population effectiveness or the underlying attack rate of were lower than 50% or 3.5%, respectively, the study would quickly become underpowered. Because of these uncertainties we plan to continue enrollment and follow-up through March 2011 (which is practically to the end of the “winter” rotavirus season) in order to assure the study will have sufficient power.

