### *Primary Aim*

*To evaluate the population (overall) (Halloran, et al., 1997) effectiveness of Rotarix in reducing rates of acute diarrhoea due to rotavirus, as detected by patients admitted to a study treatment facility, among all infants and young children from villages where Rotarix is introduced compared to among those from villages where Rotarix is not introduced.*

Main analysis, on Overall population: first episodes of rotavirus diarrhea. A Poisson regression with Pearson scale parameter (calculated at the village level) will be fit, offset with person-years of exposure, with a dummy covariate for village randomization arm status and a dummy covariate for villages in the Matlab service area (corresponding to the stratified randomization).

Note that this overall effectiveness is a function of vaccine efficacy and vaccine coverage. Since over 90% coverage is expected, this will not be much different from a total effects analysis. Also, if there are any indirect effects that act to reduce transmission, these may exert a differential effect over time, as it is not until near the end of the study period that the entire population of children under 2 years of age will be saturated with vaccine.

Additional analysis: same as main analysis, but including **all** episodes of rotavirus diarrhea, not just first episodes. The scale parameter at the randomization unit level also accounts for all within-child correlation, so the same analysis approach can be used.

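### The primary and secondary Poisson models adjust only for service area, although villages were also stratified within area on size and baseline diarrhoea admissions, so some precision is forgone

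*SAP*

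**What the plan says.** Section numbers here follow the body of the SAP, not its table of contents.

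- **Design (SAP 2.2).** "There are 75 villages in the government comparison area and 67 villages in the intervention area", and "The villages in each area will be randomized separately". Inside each area, "villages will be randomly selected for Rotarix introduction after pre-stratifying on village size and baseline hospitalization rates/numbers for diarrhoea", with 2005 and 2006 as the baseline years. Allocation is 1:1 within strata: "For each stratum of villages, half of the villages will be randomly selected for introduction of Rotarix". The number of strata and their cut-points are not given.
- **Primary model (SAP 3.5, Primary Aim).** "A Poisson regression with Pearson scale parameter (calculated at the village level) will be fit, offset with person-years of exposure". Its covariates are the arm and "a dummy covariate for villages in the Matlab service area (corresponding to the stratified randomization".
- **Secondary models (SAP 3.5, Secondary Aims).** The total-effectiveness model has the same two dummies, and indirect analyses (a) and (b) refer back to that Poisson model.
- **Other adjustment (SAP 3.6).** Baseline covariates enter only an exploratory forward stepwise model for total effectiveness, chosen by p-value and size of rate ratio.

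**The concern.** The parenthetical shows that the authors meant the primary analysis to mirror the randomisation. The area dummy mirrors only the outer layer. Village size and baseline admissions, the two factors used inside each area, are in no confirmatory Poisson model.

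Between-village variation is the main limit on precision here: SAP 2.5.1 plans on a design effect of 3.48 and later gives 2.9 to 4.5. A village's past diarrhoea admission rate is an obvious candidate to explain part of that variation, and it is known for every village because it was needed to randomise. Leaving it out forgoes precision in a trial that SAP 2.5 itself says could quickly become underpowered if effectiveness or attack rate fell short.

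**Working it through.** **1. Design against model**

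| Factor | Used to randomise (2.2) | In the Poisson models (3.5) |
|---|---|---|
| Service area | yes | yes, dummy |
| Village size | yes, within area | no (person-years enter only as offset) |
| 2005-2006 diarrhoea admissions | yes, within area | no |

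**2. The plan's own figures (SAP 2.5.1)**

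- Inputs: mean village size 65, size CV 0.96, ICC 0.02, attack rate 3.5% in unvaccinated villages. On the effect, "we assumed 50% vaccine population (overall) effectiveness".
- Design effect: 1 + ((0.96² + 1) × 65 − 1) × 0.02 = 1 + 123.904 × 0.02 = 3.478.
- Events without clustering: exact conditional binomial, P = 0.5 against 0.5/1.5 = 1/3, two-sided 5%. The smallest total from which power stays at or above 80% is 77 (power 0.82 at 77).
- Events with clustering: 77 × 3.48 = 267.96, so 268.
- Infants: 268 / (0.035 × 0.75) = 10,210.

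All four figures reproduce. None takes credit for stratification, so the planned 80% does not rest on adjusting for it.

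**3. Room for a gain**

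At a design effect of 3.48, the share of variance that comes from clustering is (3.48 − 1)/3.48 = 0.71. If log baseline rate has correlation r with the village rotavirus effect, adjustment can remove at most about 0.71 × r² of the variance:

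- r = 0.3: 6%
- r = 0.5: 18%
- r = 0.7: 35%

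The realised gain is smaller, because stratified allocation has already balanced part of this between the arms. The SAP does not give r.

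**4. Simulated gain**

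All runs used 142 villages, ICC 0.02, size CV 0.96 and stratified allocation. Absolute SDs differ between sets of runs, so compare only within a row.

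| Assumed r | SD of log RR, unadjusted to adjusted | Fall in variance |
|---|---|---|
| 0 | 0.196 to 0.195 | 1 − (0.195/0.196)² = 1% |
| 0 | 0.239 to 0.238 | 1% |
| 0.5 | 0.189 to 0.183 | 6% |
| 0.5 | 0.198 to 0.188 | 10% |
| 0.5 | 0.226 to 0.214 | 10% |
| 0.7 | 0.183 to 0.171 | 13% |
| 0.7 | 0.189 to 0.171 | 18% |
| 0.7 | 0.217 to 0.197 | 18% |

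At r of 0 to 0.3 there was no material gain, and no penalty at 0. With stratum dummies (8 strata per area assumed) explaining 25% or 50% of the between-village variance, SD went from 0.202 to 0.194 and from 0.188 to 0.181, a fall in variance of 8% and 7%.

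**5. The SAP's own standard error**

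A Pearson scale calculated over villages weights them equally, so under the planning inputs it averages about 1 + (65 − 1) × 0.02 = 2.28, against a true inflation of 3.48. The standard error is then too small by a factor √(3.48/2.28) = 1.235. A nominal 1.96 becomes 1.96/1.235 = 1.587, which is a two-sided error of about 11%.

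Simulation agrees. With no stratum effect the SD was 0.206 and the mean model SE 0.163. Type I error was about 8-11% unadjusted and 10-12% adjusted.

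**The case against.** Much of the case for leaving the model alone stands.

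- **The gain may be small.** The baseline measure counts diarrhoea of any cause in 2005-2006, and the outcome is rotavirus diarrhoea in 2008-2011. No document gives their correlation, and at 0-0.3 nothing material is lost.
- **Part is already handled.** The area dummy absorbs a roughly twofold difference in rates (18.5 against 37.3 per 1000 in infants under 12 months), and the offset handles exposure due to size.
- **Adjustment alone can worsen inference.** With the Pearson scale kept, adding the two covariates at r = 0.7 moved type I error from 7.8% to 10.5%, because the model SE fell (0.166 to 0.142) by more than the true SD (0.185 to 0.169).

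Three stronger readings are tempting, and the document does not support them.

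- **The unadjusted intervals are too wide.** Under a valid clustered variance they are (type I error 2.5-3.9% at r of 0.5-0.7). The SAP specifies the village-level Pearson scale, under which they come out too narrow.
- **The benefit of stratifying is lost.** It is not: in simulation the unadjusted SD fell from 0.204 to 0.185 as r rose from 0 to 0.7, through balanced allocation alone.
- **Far fewer events would have sufficed.** If the strata explained 25% of the extra variance, the scale would be 1 + 2.48 × 0.75 = 2.86 and the events 77 × 2.86, so 221 instead of 268. That sum treats the Pearson scale as equal to the design effect and ignores the balance already gained.

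None of this justifies describing the area dummy as the stratified randomisation, or omitting design factors without a reason.

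**Conclusion.** The mismatch between SAP 2.2 and 3.5 is plain on the page: the parenthetical is wrong as a description of the stratification, and two of the three stratifying factors are missing from the primary and secondary Poisson models. The consequence is moderate and conditional. Adjustment would lower the variance of the log rate ratio by about 6-18% if r is 0.5-0.7, and by little or nothing if r is 0-0.3. These figures rest on the SAP's ICC and size CV, on the assumed r, and on assumed strata, since 2.2 does not define them. Planned power is not undermined, and the point estimate keeps the balance from allocation. The change is worth making because it could help and costs almost nothing, provided that the variance estimator is changed with it.

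**What to change.** 1. In SAP 3.5, add the within-area randomisation strata to the primary and secondary Poisson models, alongside the arm and area dummies. If the strata are too sparse for indicators, use log village size and log 2005-2006 diarrhoea admission rate as two continuous covariates. State in advance how a village with no baseline admissions enters the log rate.
2. Replace the village-level Pearson scale for inference with a village-clustered robust variance with small-sample correction, such as Mancl-DeRouen. In simulation the adjusted model then had type I error of 4.3-6.1% at r of 0.5-0.7.
3. Correct the parenthetical to say that the area dummy represents the separate randomisation by area, and name the within-area strata as further terms. If they are left out, give the reason.

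The cost is SAP wording and two or a few degrees of freedom out of 142 villages. The baseline data are those already compiled for randomisation, and SAP section 1 says that the plan was being finalised without knowledge of results by arm, so the terms could be pre-specified cleanly.

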### *Secondary Aims*

*1. To evaluate the total effectiveness of Rotarix in reducing rates of acute diarrhoea due to rotavirus, as detected by patients admitted to a study treatment facility, among vaccinated infants and young children from villages where Rotarix is introduced compared to unvaccinated infants and young children from villages where Rotarix is not introduced.*

Main analysis, “overall effectiveness” primary analysis population: with the modification of starting observation time at 12 weeks instead of 6 weeks of age. A Poisson regression with Pearson scale parameter (calculated at the village level) will be fit, offset with person-years of exposure, with a dummy covariate for village randomization arm status and a dummy covariate for villages in the Matlab service area.

Additional analyses:

- a. As in 1., but for all (not just first) cases of rotavirus diarrhea.
- b. As in 1. and 1.a, but for the mITT population.

*2. To evaluate the indirect effectiveness of Rotarix in reducing rates of acute diarrhoea due to rotavirus, as detected by patients admitted to a study treatment facility, among unvaccinated*

*infants and young children from villages where Rotarix is introduced compared to those from villages where Rotarix is not introduced.*

*Analyses are given according to the populations a, b, c given above.*

a) Those aged at least 20 weeks as of Nov 1, 2008 (Apr 1, 2009), with censoring at earliest of 2 years of age or Mar 31, 2001, whichever comes first. Also included are those who in-migrate between ages 20 weeks-2 years. Poisson regression as described above will be used; all cases (first and subsequent) will be used.

b) Those in the Overall population, but with censoring at first OPV dose. Because of the high coverage, this will not comprise many person-years. Poisson regression as described above will be used; all cases (first and subsequent) will be used.

c) All person-time contributed by infants or children who were between 6 weeks and 2 years of age at some point during the study period.

A detailed, yet “black box” analysis will use a Cox regression model with calendar timeline, with baseline hazard stratified by age at entry: 6wks-6 months, 6 months-1 year, 1yr-2yrs. The first step is to determine, for each village, for each day of the study, the time-varying proportion of infants and young children (6wks to 2 years) who have received at least 1 dose of OPV. Then, for each village, we find the 3 dates corresponding to when the village first achieves the proportions: 0.25, 0.50, 0.75. Thus, at any point in time, we can categorize each village into one of four immunization coverage categories: 0-24%, 25-49%, 50-74%, and 75-99%. There may be some misclassification in that a village may reach 27% one day and drop to 20% a month later, but these variations will be too difficult to track, and should not have much effect.

Crossing these four categories with whether a village is a Rotarix or control village yields 8 time-varying categories, which can be represented by 7 covariates:

$$R_{it}^{0-24}, R_{it}^{25-49}, R_{it}^{50-74}, R_{it}^{75+}, C_{it}^{25-49}, C_{it}^{50-74}, C_{it}^{75+}$$

where  $R$  and  $C$  correspond to Rotarix and control villages, respectively,  $i$  is for the  $i$ th infant, and  $t$  is for the infant's age in days. For example, if a given infant living in a Rotarix village is 87 days old on a given day, and on that day the village has already reached 25% coverage but not yet 50% coverage as defined above, then  $R_{it}^{25-49} = 1$  and the other 7 covariates are coded as 0.

Note the reference category is 0-24% coverage in a control village. In addition, we will track the immunization status of each infant with the variable  $Vac_{it}$  which starts as 0 and becomes 1 upon first OPV. This variable is not of much interest—its coefficient will estimate any protective effect due to selection for vaccination. Crossing this term with village type of residence, denoted by  $X_i$  ( $=1$  for Rotarix,  $0$  for control) yields an interaction term that indicates the individual-level protection afforded by Rotarix. Putting this all together into a specification of the hazard function, we get:

$$\lambda_i(t) = \lambda_0(t) \exp(\beta_1 Vac_{it} + \beta_2 X_i Vac_{it} + \beta_3 R_{it}^{0-24} + \beta_4 R_{it}^{25-49} + \beta_5 R_{it}^{50-74} + \beta_6 R_{it}^{75+} + \beta_7 C_{it}^{25-49} + \beta_8 C_{it}^{50-74} + \beta_9 C_{it}^{75+})$$

where  $\lambda_0(t)$  is the unspecified baseline hazard function.  $X_i$  does not appear by itself because there is no expected effect of whether a child lives in a Rotarix or control village *per se*, as that was determined through randomization.

The indirect effects at any given level of coverage are estimated by taking the difference of the relevant covariates. For example,  $\exp(\beta_6 - \beta_9)$  gives the relative hazard of those in a highly Rotarix-immunized village compared to those in a highly OPV-only immunized village. Note there will not be a great deal of power for these comparisons, however.

It will also be advisable to add two time-varying dummy variables to track the three main seasons (see the seasonality discussion below).

The best way to analyze these data is to use a gamma frailty model that assigns a random intercept term to each village to account for within-village correlation. Stata has a function for this, although it will take some careful work to split up each child's observation time into a number of intervals to account for all the time-varying covariates. It may also be possible to use the SAS PROC SURVEYPHREG to estimate a robust variance to account for the correlation. The advantage to this approach is that SAS allows for continuously-varying time-varying covariates that are relatively easily coded. If this specification in SAS, that will be the preferred approach for analysis.

*3. To evaluate the direct effectiveness of Rotarix in reducing rates of acute diarrhoea due to rotavirus, as detected by patients admitted to a treatment facility, among vaccinated infants and young children from villages where Rotarix is introduced compared to unvaccinated infants and young children from villages where Rotarix is introduced.*

This direct effect is best estimated by  $\beta_2$  in the above model, which is the remaining effect of Rotarix after accounting for the indirect effects. This will be run for the mITT population.

A second estimate will be provided by applying a Cox model to the Direct effect population (i.e. the mITT population only in Rotarix villages), with a time-varying covariate for receipt of first dose of Rotarix.

*4. To investigate the overall, total, indirect, and direct effectiveness of Rotarix in reducing rates of acute diarrhoea due to rotavirus and requiring at least one overnight stay and rehydration therapy (equivalent to WHO plan B or C) in a treatment facility* Perform the above analyses, but for this severity definition.

*Two more definitions for severe diarrhea analyses will be used in each analysis:*

- 1) Acute rotavirus diarrhea scoring Vesikari 11 or greater
- 2) Acute rotavirus diarrhea scoring Vesikari 15 or greater

Thus, we have a total of four effectiveness parameters according to varying degrees of severity: the above three, and the first definition of any acute rotavirus diarrhea.

*5. To investigate the direct effectiveness and total effectiveness of Rotarix in reducing rates of all-cause acute diarrhoea, as detected by patients admitted to a treatment facility.*

Same as above, but not restricted to rotavirus diarrhea or to first case.

*7. Immunogenicity analyses: The proportions seroconverting after receipt of both doses will be calculated and compared. Reverse cumulative distribution curves will be drawn.*

*If there is a 3.5% cumulative incidence of rotavirus diarrhea, and 50% vaccine effectiveness, we expect only about 8 cases of rotavirus diarrhea in the immunogenicity subset, not enough to explore incidence as a function of immune response.*

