## 2.5 Sample Size Considerations

### 2.5.1 Sample size calculations

The primary study endpoint will be admission for rotavirus gastroenteritis (see definitions, section 2.3.8). From 2003 to 2006 the average annual rotavirus admission rate to the Matlab Diarrhoeal Hospital among infants 0 to 11 months of age from the government comparison area was about 18.5 per 1000 and among infants 12 to 23 months of age it was 12.3 per 1000 (Table 3a); among infants 0 to 11 months of age from the intervention area it was 37.3 per 1000 and among infants 12 to 23 months of age it was 24.5 per 1000 (Table 3b). Because we will conduct surveillance among age-eligible infants continuously from study initiation, infants enrolled early will fall under longer surveillance while infants enrolled later will fall under brief surveillance (for example, only a few months). Additionally, because enrolment and surveillance for rotavirus diarrhoea will occur in the government comparison area and intervention area along different timelines, we used modeling to estimate a total study-period rotavirus diarrhoea hospitalization rate of 33 per 1000 infants (3.3%) (data not shown). With inclusion of infants admitted for rotavirus gastroenteritis at the Nayergaon and Kalirbazaar Community Treatment Centres, this rate may be slightly higher at 3.5%.

Because this is a cluster-randomized design, we must account for the intracluster (intra-village) correlation of acute rotavirus gastroenteritis. At the time of study planning, this value is not available for the study population. However, given the ubiquitous nature of rotavirus, we expected this value to be low (we assumed 0.02). Additionally, because we predefine clusters as villages for this study, we cannot set the cluster sizes to be equal; villages from the government comparison and intervention areas vary substantially in size (numbers of annual births). According to the timelines for enrolment for the 142 villages in from each area, the average cluster size is expected to be 65 with a coefficient of variation of cluster sizes is 0.96. Factoring in these values, along with the assumed intracluster correlation coefficient, into the calculation of the design effect for a cluster-randomized trial (Eldridge, 2006), we calculate a design effect of 3.48. Later estimations of the design effect based on rotavirus admission data for Matlab hospital place the design effect in the range of 2.9 to 4.5.

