|                                             | 
Three groups are definable for analysis of indirect effects.
 
Indirect Population 1
 
Those included: Infant and child residents of Matlab who are at least 20 weeks of age as of Apr 1, 2009 (ICDDR,B service area villages) or Nov 1, 2008 (Govt service area villages) or in-migrants to the study area who are between 20 weeks and 2 years of age during the study period. Treatment group assignment for these children will be determined by village of residency at the time that first allows them to be included in this population.
 
Follow-up period: Person-time will be counted from Apr 1, 2009 (ICDDR,B service area villages) or Nov 1, 2008 (Govt service area villages) or date of in-migration until two years of age (731 days) of age or March 31, 2011, whichever comes first.
 
Indirect Population 2
 
Those included: Infants who resided in Matlab between 6 and 20 weeks of age after Apr 1, 2009 (ICDDR,B service area) or after Nov 1, 2008 (Govt service area).
 
Follow-up period: Person-time will be counted from Apr 1, 2009 (ICDDR,B service area villages) or Nov 1, 2008 (Govt service area villages) or date of in-migration until receipt of OPV1, the child turns two years of age (731 days), or March 31, 2011, whichever comes first.
 
Indirect Population 3
 
Those included: All infants or children resident of the study area aged between 6 weeks and 2 years at some point during the study period.
 
Follow-up period: All person-time contributed during the study period. The analysis will account for receipt of vaccine (this will include any
 |

|  |                                                                                                |
|--|------------------------------------------------------------------------------------------------|
|  | indirect effects that also accrue to those who receive Rotarix, which is not 100% protective). |
|--|------------------------------------------------------------------------------------------------|

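### Indirect analysis 2(b) ends follow-up at OPV1 without adjusting for age, so an arm difference in OPV1 uptake or timing would bias its rate ratio

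*SAP*

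**What the plan says.** SAP section 3.5, Secondary Aims, item 2(b), defines the analysis set as "Those in the Overall population, but with censoring at first OPV dose". Section 3.2 (Indirect Population 2) runs follow-up "until receipt of OPV1, the child turns two years of age (731 days), or March 31, 2011, whichever comes first". A child who never receives OPV1 therefore stays in the analysis to age 2 or study end.

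The method in 2(b) is "Poisson regression as described above will be used; all cases (first and subsequent) will be used". The model referred to is the one under the Primary Aim: a person-years offset, a village-level Pearson scale, and terms "with a dummy covariate for village randomization arm status and a dummy covariate for villages in the Matlab service area". It has no age term.

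The SAP expects little data here: "Because of the high coverage, this will not comprise many person-years". Its only coverage figure is under the Primary Aim: "Since over 90% coverage is expected, this will not be much different from a total effects analysis". It gives no OPV1 uptake by arm, no distribution of age at OPV1, and no rotavirus rates by age within infancy.

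**The concern.** Randomisation balances age between arms for follow-up that ends by calendar date or birthday. It does not do so when follow-up ends at something that happens after allocation and may be affected by it. Under 2(b) an infant who receives OPV1 contributes only the interval from 6 weeks of age to that dose. One who never receives it contributes time at all ages up to two years. Each arm's crude rate is a weighted average of these two kinds of time, and the weights are that arm's OPV1 uptake and timing.

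A route to an arm difference exists. Section 2.1 puts an added vaccine and study staff into EPI sessions in Rotarix villages and leaves control villages as they would otherwise be, and section 2.2 states that the evaluation is not blinded. If uptake or timing did move, 2(b) could show an indirect effect, or hide one, with no change in transmission.

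**Working it through.** The SAP states no figure for 2(b), so there is none to reproduce. The check asks what ratio the planned model returns when the true indirect effect is nil.

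**Inputs from the SAP.** Annual rotavirus admission rates in section 2.5.1: "among infants 0 to 11 months of age from the government comparison area was about 18.5 per 1000", against 12.3 in the second year of life; for the other area, 37.3 and 24.5 per 1000. Area start dates 1 November 2008 and 1 April 2009; end 31 March 2011; follow-up to 731 days; 5825 infants per group.

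**Assumptions not in the SAP.** Infants reach 6 weeks uniformly over each area's window. Rotarix/control OPV1 uptake is 97/92, 98/95, 95/90, 95/85 or 99/95%. Delay from 6 weeks to OPV1 is exponential with mean 14, 28 or 42 days. The rate under 14 weeks is 1.0, 0.5, 0.25 or 0.1 of the rate in the rest of infancy, with the infant average held at the stated value.

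**Formula.** Crude arm rate = (never-OPV person-years × their rate + pre-OPV1 person-years × their rate) / total person-years.

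**Worked case on the SAP's rates** (government area, flat within infancy, mean delay 28 days, uptake 95% v 90%). A never-OPV infant gives 1.149 person-years at an average of 16.2 per 1000, a mix of 18.5 and 12.3. An OPV1 recipient gives 0.0756 person-years at 18.5.
- Rotarix: (0.05 × 1.149 × 16.2 + 0.95 × 0.0756 × 18.5) / (0.0574 + 0.0718) = 17.48.
- Control: (0.10 × 1.149 × 16.2 + 0.90 × 0.0756 × 18.5) / (0.1149 + 0.0680) = 17.05.
- Ratio 1.02, with identical age-specific rates in both arms.

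**Range over both areas, all delays and all uptake pairs** (Rotarix uptake higher in each; the direction reverses if control uptake is higher):

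| Rate under 14 weeks ÷ rest of infancy | False crude ratio |
|---|---|
| 1.0 (SAP rates, flat) | 1.02–1.05 |
| 0.5 | 0.84–0.96 |
| 0.25 | 0.67–0.91 |
| 0.1 | 0.52–0.87 |

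Timing alone (mean delay 14 days in Rotarix villages v 28 in control, 95% uptake in both) gives 0.98–1.10.

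**Hand check that the gradient sets the direction.** Take never-OPV shares u of 4% (Rotarix) and 6% (control), OPV1 after g = 4/52 year, one year of follow-up if never given, and early rate k times the later rate. Relative arm rate = [(1−u)gk + u] / [(1−u)g + u].
- k = 0.5: 0.676/0.727 = 0.93.
- k = 1: 1.00 exactly.
- k = 1.5: 1.324/1.273 = 1.04.

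**Share of cases from never-OPV infants**, over all assumed delays and gradients: 47–95% at 90% uptake, 30–90% at 95%, 20–85% at 97%, 8–64% at 99%.

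**Precision.** With 90–95% uptake, mean delay 28 days and gradient 0.25, about 9 to 26 cases per arm are expected. The lower figure treats all 5825 infants as government-area infants, the upper as ICDDR,B-area infants. The 95% limits are exp(±1.96√(2/n)), a factor of about 2.5 (n = 9) to 1.7 (n = 26) either way before any design effect.

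**Effect of an age factor.** With bands that follow the true rate changes and equal age-specific rates, the adjusted ratio is 1.00. A single cut at 20 weeks is coarser. For band b let E be expected cases and P person-time in each arm (R, C). The fitted ratio θ solves Σ[E_Rb − (E_Rb + E_Cb) θP_Rb/(θP_Rb + P_Cb)] = 0. Over the scenarios in the table, θ is 1.00–1.01, 0.95–1.01, 0.90–1.01 and 0.84–1.00 respectively. Most of the bias goes, but not all of it under the steepest assumed gradients.

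**The case against.** The strongest reply is that the problem is conditional and small. No arm difference in OPV1 uptake or timing is documented. The SAP already warns that 2(b) has few person-years. It is one of three analyses under a secondary aim, and random error exceeds the bias in most scenarios. Analysis (c) stratifies the baseline hazard by age at entry and models OPV status over time, which partly controls for age. All of this stands and sets the severity. It does not remove the flaw: imprecision does not correct a bias, and 2(b) itself adjusts for neither age nor selection.

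Two stronger readings are tempting. A reader might infer that never-OPV infants supply most of the cases. That depends on uptake and delay the SAP does not give: it is likely near 90% uptake, uncertain at 95%, and fails in most scenarios at 99%. A reader might also infer that the analysis will manufacture an indirect effect. That needs rates soon after 6 weeks to be well below later ones. The SAP reports no gradient within infancy, and its two age bands show the first year with the higher rate, by about 1.5 times (18.5/12.3). A lower rate in the first weeks is not excluded, but it is an assumption.

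**Conclusion.** The point holds in conditional form. Analysis 2(b) censors at a post-randomisation event and mixes very young time with time up to age 2 in a model without age. An arm difference in OPV1 uptake or timing would bias its ratio in a direction that cannot be fixed in advance. On the SAP's rates, flat within infancy, the shift is about 2 to 5% towards hiding an effect when Rotarix villages have the higher uptake. Ratios well below 1 arise only under assumed early-infancy rates that the SAP does not state. Never-OPV infants may supply a large share of cases, but this is not established. Severity is minor. The primary analysis is not affected, because its follow-up does not stop at OPV1.

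**What to change.** In 2(b), split person-time by age and add age band as a factor to the Poisson model, keeping the village-level scale. Use coarse bands, for example under 20 weeks and 20 weeks or more, because few cases are expected. Report OPV1 uptake and age at OPV1 by arm, so that a reader can see whether the condition for bias is met. Label 2(b) as supportive.

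The cost is a few lines of SAP text and a person-time split from birth, migration and OPV dates that the analysis already needs, with slightly lower precision. Two limits should be stated. A single cut leaves some residual age imbalance if rates change steeply before 20 weeks. Age adjustment also does not remove other differences between infants who never receive OPV and the rest, a selection the SAP itself recognises in the Cox model for (c). The change should be fixed before arm-specific results are seen, in keeping with the purpose stated in SAP section 1.
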